## Abstract

**Background:**

Attenuating the neurological damage occurring after out-of-hospital cardiac arrest is an ongoing research effort. This dual-centre study investigates the neuroprotective effects of the glucagon-like-peptide-1 analogue Exenatide administered within 4 hours from the return of spontaneous circulation to comatose patients resuscitated from out-of-hospital cardiac arrest.

**Methods/design:**

This pilot study will randomize a total of 120 unconscious patients with sustained return of spontaneous circulation after out-of-hospital cardiac arrest undergoing targeted temperature management in a blinded one-to-one fashion to a 6-hour and 15-minute infusion of either Exenatide or placebo. Patients are eligible for inclusion if resuscitated from cardiac arrest with randomization from 20 minutes to 240 minutes after return of spontaneous circulation. The co-primary endpoint is feasibility, defined as the initiation of treatment within the inclusion window in more than 90 % of participants, and efficacy, defined as the area under the neuron-specific enolase curve from 0 to 72 hours after admission. Secondary endpoints include all-cause mortality at 30 days and Cerebral Performance Category as well as a modified Rankin Score at 180 days. The study has been approved by the Danish National Board of Health and the local Ethics Committee and is monitored by Good Clinical Practice units. The study is currently enrolling.

**Discussion:**

This paper presents the methods and planned statistical analyses used in the GLP-1 trial and aims to minimize bias and data-driven reporting of results.

**Trial registration:**

1) Danish National Board of Health, EudraCT 2013-004311-45. Registered on 25 March 2014.

2) Videnskabsetisk komité C, Region Hovedstaden, No. 45728. Registered on 29 January 2014.

3) Clinicaltrial.gov, NCT02442791. Registered on 25 of January 2015.

**Electronic supplementary material:**

The online version of this article (doi:10.1186/s13063-016-1421-2) contains supplementary material, which is available to authorized users.

## Background

While the mortality after out-of-hospital cardiac arrest (OHCA) has improved over the last decade, mortality remains as high as 90 % [1], and even after successful resuscitation and admission to an intensive care unit (ICU), the in-hospital mortality is 30–50 % [2, 3]. Anoxic brain injury remains the leading cause of death in these patients [4]. The mechanisms causing neurological damage are complex but involve both ischemia and reperfusion injury leading to tissue degeneration and loss of neurological function, the extent of which depends on duration and density of the insult [5]. Targeted temperature management (TTM) may attenuate this damage in an experimental setting [6–9], and clinical trials have shown promising results in improving neurological function and survival [10, 11]. Despite this, the optimal target temperature is debated [12], and active neuroprotection in addition to temperature management seems intuitively beneficial. Glucagon-like peptide-1 (GLP-1) analogues are approved for the treatment of type 2 diabetes but have recently been suggested to ameliorate degenerative neurological disease and reduce inflammation after ischemic cerebral stroke [13]. The GLP-1 analogue Exenatide has been shown to reduce infarct volume after focal brain ischemia in mice [14] and to reduce infarct size in a model of acute myocardial infarction (MI) and reperfusion in swine [15]. In humans, patients treated with Exenatide after MI have been shown to have a larger salvage index assessed by cardiac magnetic resonance imaging (MRI) after 3 months [16, 17]. These findings have been confirmed by later trials [18, 19]. In addition, Exenatide has been well tolerated in acutely ill patients with ST-elevation myocardial infarction with no apparent increased risk of adverse events, including hypoglycaemia or pancreatitis, compared to placebo [17].

The present trial will investigate the neuroprotective capabilities of the GLP-1 analogue Exenatide administered for 6 hours and 15 minutes within 4 hours after the return of spontaneous circulation (ROSC) in comatose patients resuscitated from OHCA.

## Methods/design

This pilot study is a double-blind, randomized, placebo-controlled, clinical trial assessing the effect of Exenatide compared with placebo on top of TTM in adult comatose OHCA patients. Patients are enrolled at two tertiary Danish university hospitals offering highly specialized cardiac care for a population of approximately 3,000,000 citizens.

### Trial procedure

PHASE 1 (hospital admission to start of intervention): Unconscious patients who have been admitted to the hospital with sustained ROSC after OHCA are eligible for screening. The inclusion window is 220 minutes, i.e. from 20 minutes after ROSC (defined as ‘sustained ROSC’) until 240 minutes after ROSC. The patient’s eligibility for trial inclusion is assessed according to inclusion and exclusion criteria (Table 1). If all inclusion criteria and no exclusion criteria are met, informed consent is obtained, in accordance with Danish legislation, from two independent medical doctors not involved with the trial. Patients are then randomly allocated to active study drug or placebo via an internet-based randomization algorithm available on the trial website. Baseline characteristics are obtained.

**Table 1 Tab1:** Inclusion and exclusion criteria

Inclusion criteria
1. Age ≥ 18 years
2. OHCA of presumed cardiac cause
3. Sustained ROSC, defined as ROSC when chest compressions have not been required for 20 consecutive minutes and signs of circulation persist
4. Unconsciousness (Glasgow coma scale (GCS) < 8) after sustained ROSC
Exclusion criteria
1. Conscious patient (GCS ≥ 8)
2. Female of childbearing potential, unless a negative human chorionic gonadotropin (HCG) test can rule out pregnancy within the inclusion window
3. In-hospital cardiac arrest (IHCA)
4. OHCA of presumed non-cardiac cause, e.g. after trauma, dissection/rupture of major artery or arrest caused by hypoxia (i.e. drowning or hanging)
5. Known bleeding diathesis (medically induced coagulopathy does not exclude patient)
6. Suspected or confirmed acute intracranial bleeding
7. Suspected or confirmed acute ischemic stroke
8. Unwitnessed asystole
9. Known limitations in therapy and do-not-resuscitate order
10. Known disease making 180-day survival unlikely
11. Known pre-arrest cerebral performance category score (CPC) of 3 or 4
12. > 4 hours (240 minutes) from ROSC to randomization
13. Systolic blood pressure < 80 mmHg in spite of fluid loading/vasopressor and/or inotropic medication and/or mechanical circulatory support^a^
14. Temperature on admission < 30 °C
15. Known allergy to GLP-1 analogues, including Exenatide
16. Known pancreatitis
17. Known ketoacidosis
18. Uncorrected blood glucose at admission < 2.5 mmol/l

^a^If systolic blood pressure is recovering during the inclusion window, the patient can be included

PHASE 2 (duration of intervention): Phase 2 starts when the study drug/placebo administration is initiated, most often coinciding with the initiation of TTM. Patients are sedated and mechanically ventilated. Patients are treated for 24 hours with an automated-feedback device with temperature control to achieve a target core temperature (bladder) of 36 °C. After 24 hours of TTM, patients are rewarmed to a core temperature of 37 °C with no more than 0.5 °C per hour. Phase 2 ends when sedation is withheld.

PHASE 3 (from end of intervention period to 72 hours after end of intervention period): Sedation is stopped or tapered after rewarming when temperature is at least at 37 °C. Normothermia of 37 °C +/−0.5 °C is maintained until 72 hours from cardiac arrest if the patient is still managed in the ICU and is comatose or sedated. However, weaning from ventilation will be attempted at the earliest possible time during this phase based on standard procedures for the discontinuation of mechanical ventilation. Blood is drawn at 24, 48 and 72 hours and is later analysed for the biomarkers neuron-specific enolase (NSE) and S100B – markers of cerebral injury. Neurological evaluation of patients who remain in a coma is performed by blinded physicians at 72 hours or later after the end of the intervention period.

PHASE 4 (72 hours after the end of the intervention period to 28 days after OHCA): Neurological status according to the Cerebral Performance Category scale (CPC-scale) [20], and vital status are evaluated daily in the ICU on days 1, 2, 3, 4, 5, 6 and 7 and/or at hospital discharge, whichever comes first.

PHASE 5 (hospital discharge/day 28 to end of trial): Vital status and neurological status are evaluated on days 30 and 90 and then by telephone interview on day 180. The evaluation is performed by a research nurse blinded to the intervention allocation. Vital status will be assessed at the end of the trial using the Danish civil registration system. See attached Additional file 2.

### Inclusion

Patients with sustained ROSC after OHCA are eligible for inclusion if fulfilling the criteria displayed in Table 1.

### Study drug administration

Preparation of study drug (Exenatide/placebo): Trained hospital nurses not taking part in the management of the patient will prepare infusion bags with Exenatide or placebo. At first notice of a potential candidate for inclusion in the trial, a set of study drug and placebo will be prepared. The infusions will be prepared as follows:

First, 1.5 ml is removed from 250 ml of isotonic NaCl and 1.5 ml of 20 % human albumin is added to prevent binding of the study drug to the infusion material. For every potentially eligible patient, two infusion kits will be prepared. One is a placebo kit as described, and one has 25 μg Byetta (Lilly, Exenatide) added. The two infusion kits are labelled ‘A’ or ‘B’ by random allocation in a computer-based randomization system and brought directly to the ICU. The random allocation will occur via the trial website with a specific logon for personnel involved in study drug preparation. The allocation ‘A’ and ‘B’ will be chosen at random by the trial website algorithm (randomization generated into dynamic blocks), stratified for site and will be unblinded by the end of trial.

The cardiologist responsible for the patient’s treatment screens the patient’s eligibility and obtains informed consent from legal representatives. If the patient is eligible for inclusion and informed consent is obtained from two independent physicians, the patient is randomized via the trial website to receive either infusion kit ‘A’ or ‘B’, and the other kit is discarded. The cardiologist orders the infusion to be given. The infusion is given in a central or peripheral intravenous line. The nurses preparing the infusion kits remain blinded to participant allocation, and the nurses initiating the study drug infusion (ICU nursing staff) remain blinded to the preparation of the infusion kits.

The study drug infusion is initiated by the ICU nursing staff as soon as possible at a rate of 72 ml/hour (0.12 μg Exenatide/minute) for 15 minutes (volume to be infused is 18 ml), followed by 26 ml/hour (0.043 μg Exenatide/minute) for an additional 6 hours (volume to be infused: 156 ml). This concludes the pharmacological intervention and thus a total of 17.4 μg of Exenatide is administered. As the allocation is blinded, the same infusion rates are used in the placebo arm. For safety reasons, blood glucose is monitored closely during the administration period and for the following 2 hours. Blood glucose and corrective glucose administration is reported. Additional management of the patients is at the discretion of the attending physicians. Thus, all trial participants, care providers, investigators and outcome assessors remain blinded to the intervention until completion of the trial. If a suspected unexpected serious adverse reaction (SUSAR) is found, the sponsor has the ability to unblind the patient’s intervention allocation through the physician responsible for the trial website, who is otherwise detached from the trial.

#### Monitoring of compliance

Infusion of study drug ‘A’ or ‘B’ will be recorded along with time of initiation of the study drug infusion. In addition any dose reduction or interruption of administration will be recorded. Reasons for not infusing the study drug per protocol and any dose reduction outside of ± 5 minutes from the scheduled time point are registered. Suspected adverse events, as well as the actions taken to correct these and their consequences, are recorded.

### Concurrent medication/treatment

Computed tomography of the brain/neck/head will only be performed as clinically indicated, not as a routine screening after admission. Patients will be treated with standard therapies for cardiac diseases. Coronary angiography, percutaneous interventions and/or open-heart surgery will be performed according to current guidelines at the discretion of the treating physician. Necessary cardiac interventions will not be delayed by the trial intervention; however, efforts will be made to maintain the study drug infusion and TTM during treatment.

### Logistics

The study is enrolling at two tertiary centres with experience in conducting clinical trials. All investigators have been trained and ‘good clinical practice’ (GCP) certified. Other involved personnel (i.e. ICU nurses) have been trained in their specific roles.

### Endpoints

The co-primary endpoints are as follows:Feasibility, defined as > 90 % initiation of study drug administration within 4 hours following ROSC in patients eligible for inclusionEfficacy, defined as the area under the NSE curve from admission to 72 hours post-admission. Missing data will be imputed.

Secondary endpoints are as follows:Area under the S100B curve with daily measurements until 72 hours, and absolute NSE and S100B values at 48 hours. Missing data will be imputed.Composite outcome of all-cause mortality and poor neurological function, defined as the modified Rankin Scale (mRS) 4–6 at 30 days (telephone assessment)Vital status at 7 days and at least 180 days (end of the study) after OHCA by registry-based follow-upAssessment of CPC and mRS at 90 daysArea under the creatine kinase MB (CK-MB) and troponin T curve from 0 to 24 hours. Missing data will be imputed.Safety, defined as the cumulated incidence of serious adverse events (SAE) related to the study drug: death, need for mechanical hemodynamic support, hypoglycaemia < 3.0 mmol/l, pancreatitis (S-amylase > 3 UNL), need for renal replacement therapy in the first 3 days. In addition, hypoglycaemia and pancreatitis will be reported separately as additional safety.

Tertiary endpoints are as follows:Left ventricular ejection fraction on last in-hospital echocardiography, stratified by the presence of acute myocardial infarction as the cause of cardiac arrest. Patients dying during the index administration in whom a post-TTM echocardiography is not available will be given the lowest LVEF score seen in each allocation group. Missing data will be imputed.Presence of EEG findings associated with poor prognosis and EEG performed as part of per-protocol prognosticationVital status at 180 days and telephone-based CPC and mRS at 180 daysVital status at 180 days stratified for cause of death (i.e. neurological versus cardiovascular and other – will be adjudicated by two intensive-care consultants blinded to treatment allocation)

Blinded efficacy variables will be recorded at 3, 30, 90 and 180 days. The telephone-based assessment will be performed by a single trained study nurse, not otherwise involved in the care of patients. Other variables will be assessed and recorded in the case report forms (CRF) by a trained physician not involved in the care of patients. The NSE and S100B plasma levels will be measured in the hospital laboratory for each site and recorded in the CRF. The study drug allocation will remain blinded until all follow-up data have been recorded. All CRFs will be entered into the trial database. The quality of data entry will be evaluated by random samples as well as range checks for data values. Individual patient data will be handled as ordinary chart records and will be kept according to national legislation.

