### Sample size estimation

The primary outcome is feasibility and the area under the NSE curve (NSE AUC) at 72 hours. Since no difference in feasibility is expected and the trial is designed as a pilot study, we have chosen to power this study according to differences in the NSE AUC. A difference of 20 % is defined as the minimal clinically relevant difference. Previous studies have found a value of approximately 20 μg/ml (25–75 % CI 10–45) at 72 hours [21]. We expect a mean AUC at 72 hours of 50 μg/ml*day, assuming an SD of 30 % of the mean AUC. The α is set at 0.025 (co-primary endpoint), which gives a power of 90 % if 50 patients are included in both groups. A 10 % loss of final measurement is expected (patients expiring before full 72 hours). Therefore, we aim to include 120 patients in total.

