### Statistical analysis plan

#### General principles

The general principles for statistical analyses will be:Analyses will be performed according to the intention-to-treat principle with patients lost to follow-up included in the denominator [22].A two-sided significance level of 0.025 will be applied to the primary endpoints and 0.05 will be applied to the secondary endpoints.The two trial sites will be asked to complete all CRFs and other forms if missing data is found in the electronic database. Missing data will be reported in the publication.More than 5 % missing data in outcome variables (see Endpoints) will result in multiple imputation with the creation of 10 imputed datasets to be analysed separately and then aggregated into one estimate of the intervention’s effect on the primary and secondary endpoints [23, 24].

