##### Secondary and tertiary outcomes

Differences between treatment groups will be analysed with an independent sample *t* test or chi-Square test depending on the variable being numerical or categorical. In case of skewed data, logarithmic transformation will be applied to approximate normal distribution. Crude survival analyses stratified to the treatment groups are performed using proportional hazard models. Hazard rates will also be reported adjusted for site, sex, age, shock-able primary rhythm, and time to ROSC (logarithmically transformed). Hazard ratios will be presented with 95 % confidence intervals.

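### The 30-day composite of death or mRS 4–6 gets only a crude chi-square test, although the plan already names and collects covariates that would sharpen it: a modest, cheaply recovered loss of precision on an unpowered secondary endpoint

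*Protocol article*

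**What the plan says.** All references are to the protocol article.

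- **Endpoints.** The second item in the secondary list is the "Composite outcome of all-cause mortality and poor neurological function", with poor function set at mRS 4–6 at 30 days. A patient either meets it or does not, so it is a binary variable.
- **Secondary and tertiary outcomes.** Group differences are tested by a t test or "chi-Square test depending on the variable being numerical or categorical". No covariates enter that comparison.
- **Same paragraph, survival.** "Crude survival analyses stratified to the treatment groups are performed using proportional hazard models", and then: "Hazard rates will also be reported adjusted for site, sex, age, shock-able primary rhythm, and time to ROSC (logarithmically transformed".
- **Baseline data.** Sex, age, shockable rhythm and time to ROSC are predefined baseline variables. Site is not in that list, but the section on study drug administration names it as the randomization stratum, so it is known for every patient.
- **General principles.** "A two-sided significance level of 0.025 will be applied to the primary endpoints and 0.05 will be applied to the secondary endpoints".

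**The concern.** The plan treats five variables as worth adjusting for when the outcome is time to death. It does not use them when the outcome is death or poor function. The only covariate-adjusted clinical result will therefore concern mortality, and none will exist for survival with good function.

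The method is stated in the text, so this is a choice that can be reviewed, not a detail left to a fuller document.

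Two things are at stake. First, a logistic model that includes strong predictors of outcome usually has more power than a two-by-two table of the same patients. Second, randomization is stratified by site alone, so with 60 per arm some imbalance in rhythm, age or time to ROSC is likely. If one appears and no adjusted analysis of the composite was prespecified, any adjustment would be post hoc. The article says that it aims to avoid data-driven reporting of that kind.

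**Working it through.** **The plan's own figure.** The composite has no stated power. The only power statement concerns NSE AUC: "The α is set at 0.025 (co-primary endpoint), which gives a power of 90 % if 50 patients are included in both groups". With a difference of 20 % × 50 = 10 and an SD of 30 % × 50 = 15, the standardized difference is 10 / (15 × √(2/50)) = 3.33. At two-sided 0.025 the power is Φ(3.33 − 2.24) = 86 %; at one-sided 0.025 it is Φ(3.33 − 1.96) = 91.5 %. That mismatch is a separate matter. It is shown here only because no corresponding figure exists for the composite.

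**Inputs for the composite.**
- From the document: 120 patients randomized 1:1, so 60 per arm; two-sided 0.05 for secondary endpoints; five covariates.
- Assumed: control risk 50 %. The only anchor is the Background's in-hospital mortality of 30–50 %, to which survivors with mRS 4–5 add.
- Assumed: absolute reductions of 10 and 20 points, and joint covariate discrimination (AUC) of 0.70–0.85. The document gives neither.

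**Crude chi-square, by formula.** Power = Φ{[d − 1.96 × √(2p̄(1 − p̄)/n)] / √[(p₁(1 − p₁) + p₂(1 − p₂))/n]}, where d = p₁ − p₂, p̄ is the mean risk and n = 60.
- 50 % vs 30 %: (0.20 − 1.96 × 0.0894) / 0.0876 = 0.28, so power is 61 %.
- 50 % vs 40 %: (0.10 − 1.96 × 0.0908) / 0.0904 = −0.86, so power is 19 %.
- With a control risk of 40 % or 60 %, a 20-point reduction has 67 % or 59 % power.

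**Crude against adjusted, by simulation.** 60 per arm, 4,000 trials per setting; logistic outcome with five covariates, three prognostic and two null; adjusted result from the Wald test of treatment.

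| Covariate AUC | 50 % vs 30 %: crude | adjusted | 50 % vs 40 %: crude | adjusted | 50 % vs 50 %: crude | adjusted |
|---|---|---|---|---|---|---|
| 0.70 | 62.0 % | 66.0 % | 20.6 % | 21.6 % | 5.7 % | 5.8 % |
| 0.75 | 62.2 % | 69.6 % | 20.9 % | 22.9 % | 6.2 % | 6.5 % |
| 0.80 | 62.1 % | 72.8 % | 20.0 % | 24.4 % | 5.3 % | 5.2 % |
| 0.85 | 61.8 % | 79.0 % | 19.8 % | 26.9 % | 5.3 % | 5.1 % |

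At a 10-point reduction the Wald gain runs from 21.6 − 20.6 = 1.0 point to 26.9 − 19.8 = 7.1 points. The likelihood-ratio test gives slightly more power (67–80 % at 20 points, 22–29 % at 10 points) with a type I error of 5.4–6.9 %. The Monte Carlo standard error is √(0.62 × 0.38/4000) = 0.8 points near 62 % and √(0.05 × 0.95/4000) = 0.3 points near 5 %.

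Other runs with similar layouts agree. For 50 % vs 30 %, adjusted Wald power was 65 % at AUC 0.70 and 76–77 % at AUC 0.83. A test on the standardized risk difference gave 68–76 % at AUC 0.69–0.81.

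**Chance imbalance.** The SD of the between-arm difference in a binary covariate is √(2p(1 − p)/60). For prevalence 50 % this is 0.091, and a gap of at least 10 points has probability 2 × [1 − Φ(0.10/0.091)] = 27 %. For prevalence 80 % the SD is 0.073 and the probability is 17 %.

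**The case against.** The strongest reply is that nothing here is an error. In a 1:1 randomized comparison the chi-square test is valid and unbiased. That stands.

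- **Chance imbalance.** A reader might infer from the 17–27 % figure that the crude comparison is untrustworthy, or that imbalance could mimic an effect. The documents do not support this. False positives from chance imbalance are already inside the nominal 5 %, and the simulated crude type I error is close to that level.
- **The endpoint's rank.** A reader might also take this to be the trial's key clinical efficacy endpoint. Its place in the list shows no such rank. The Endpoints section states no hierarchy, the abstract's list of secondary endpoints does not mention the composite, and mRS and CPC at 90 and 180 days are assessed too. The trial is a pilot powered on NSE AUC, with a surrogate chosen deliberately.
- **The size of the gain.** It rests on assumptions and looks best at a 20-point reduction. At 10 points the endpoint is badly underpowered with either test, and adjustment would seldom change the conclusion.
- **The survival plan.** Crude results with adjusted ones in support is a conventional order. The plan follows it for survival, where adjusted hazards are an addition to the crude model. The documents do not show that the sponsor regards adjustment as its main analysis.
- **Partial cover.** Mortality, one component, already has an adjusted estimate, and the baseline table would reveal an imbalance.

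The asymmetry survives all of this: death has a prespecified adjusted estimate and the functional composite has none, although every variable needed is at hand.

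**Conclusion.** The point holds as a matter of efficiency, not validity. The stated test leaves unused the precision that the plan's own covariates could supply.

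With 60 per arm, an assumed 50 % control risk and covariate AUC of about 0.70–0.83, adjustment lifts power from about 62 % to about 65–77 % for a 20-point reduction. For a 10-point reduction it adds about 1–7 points, and power stays below 30 %. The outcome rate, the effect on the composite and the covariate strength are all assumptions. If the covariates predict weakly, the benefit is near the bottom of these ranges.

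This is a worthwhile low-cost improvement to an unpowered secondary endpoint and has no bearing on the primary analysis.

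**What to change.** Before unblinding, prespecify a logistic regression of the 30-day composite on treatment plus the five covariates already named for the hazard model: site, sex, age, shockable rhythm and log time to ROSC. Report the standardized risk difference with its 95 % CI, using a small-sample-corrected or bootstrap standard error, together with the conditional odds ratio. Keep the crude proportions and the chi-square test alongside.

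The cost is one extra model and a few lines of text, with no new data. The drawbacks are small:
- The odds ratio is conditional on the covariates, which is why the standardized risk difference is reported as well.
- A few missing covariate values would need simple imputation.
- Type I error may rise slightly, to about 5–7 %, without a small-sample correction. Under 50 % vs 30 % there would be 30 + 18 = 48 events for six coefficients beyond the intercept, or 48/6 = 8 per coefficient, so the correction is worth specifying.
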